## **3.5 Treatment Assignment Procedures**

### **3.5.1 Randomization Procedures**

Individual participants will be randomized to receive either 30µg or 100µg of GMZ2 or rabies vaccine. Randomization to any of the three groups will be done based on a list of eligible participants identified after screening is completed. The randomization list generated by the statistician will ensure that the random allocation has a fairly even distribution of sex and age in the groups. The randomization list will contain sequential codes linking a study number to a vaccine assignment. Study numbers will be assigned to participants of each cohort in the order in which they are enrolled in the trial. Access to the randomization list will be exclusively limited to the vaccine administrator/pharmacist(s) and the study statistician. These individuals will be unblinded and will not be involved in any of the study participants' evaluation. The independent Local Safety Monitor will also keep one set of the randomization code in a sealed envelope, for the event when emergency unblinding may be required.

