## 6.2 Safety Monitoring Plan

### 6.2.1 Role of the Safety Monitor:

The Local Safety Monitor (LSM) will be an experienced clinician qualified to evaluate safety data from clinical trials of vaccines. He/she will not be directly involved in the clinical trial and will be based in Lambaréné. All SAEs will be reported to him/her. In exceptional circumstances, for example a death possibly related to vaccination, or under conditions as outlined in below in the safety monitoring plan, he/she will have the authority to suspend vaccination pending discussion with the sponsor and collaborators. He will hold the code-break information and under conditions as outlined below, he will have the authority to unblind individual subjects. All unblinding should be reported immediately to AMANET. The LSM will also pass on his reports to the Data Safety Monitoring Board (DSMB) regularly, during the process of the trial.

Thus the LSM's role will include:

- Acting as the study participants' advocate
- Promptly communicating relevant safety information to the DSMB
- Providing advice to the investigators on whether a set of clinical circumstances in a study warrants formal notification to AMANET and DSMB
- Providing clinical advice on any illness in study participants especially in circumstances in which treatment might influence the course of the trial
- Review all SAEs as outlined above

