### 6.2.3 Holding Rules

Vaccination will be performed in a randomised plan. After each vaccination, safety data will be provided in tables by the data manager. The safety tables will be reviewed by the DSMB in a blinded manner.

If there are no safety issues noted, the study will proceed as planned. However, if based on the review of the safety data tables provided, 50% of participants in a particular are found to have developed a Grade 3 adverse event, related to vaccination and persisting at Grade 3 for > 48 hours during the 14 follow-up days after vaccination, a decision of individual un-blinding may then be made by DSMB through the Local Safety Monitor. Subsequent vaccination of that group will be put on hold pending discussion with the investigator, and the sponsor.

Within five working days of the Local Safety Monitor placing vaccination of a group on hold, the Sponsor will organise a meeting (via teleconference, or face-to-face) to review and discuss the safety data and the events leading to the hold order. At least two working days prior to this meeting, the Sponsor will disseminate copies of all relevant safety data to all meeting participants.

**Activation of the Holding Rules requires a thorough review by the DSMB of blinded reactogenicity and safety data and discussion with the investigator, and the sponsor.**

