## 7 EVALUATION CRITERIA

### 7.1 Primary Evaluation Criterion: Safety

#### 7.1.1 Definition of the Criterion

The safety profile will be assessed on the following criteria:

- Immediate reactogenicity (reactions within 30 minutes after each injection),
- Local and systemic reactogenicity measured from Day 0 to Day 14 after each dose
- Any unsolicited adverse event resulting in a visit to a physician between each injection and one month after the third dose.
- Any Serious Adverse Event (SAE) occurring from the inclusion through out the study. The relationship of the adverse event to the study vaccine will be established by the investigator, using the following definitions: related or not related.
- Biological safety, one month after each vaccination, in reference with the baseline before the first dose, by measuring the following:
  - RBC, haemoglobin, haematocrit, platelets, total WBC;
  - serum creatinine, ASAT, ALAT, total bilirubin, alkaline phosphatase.

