### 8.3 Data Set to be analysed

#### 8.3.1 Definition of Population

Given the above mentioned considerations it is planned to enrol 30 participants in the trial, to be randomised into the three treatment arms.

The statistical analysis shall be performed on two types of population depending on the participant's compliance to the protocol:

**i). Per Protocol:** the vaccination, blood sampling and visits number as well as the time-interval between vaccination and follow-up visits are respected, as they are defined in the protocol and in the flow chart. All participants who have not been compliant with the protocol will be excluded from this analysis but will be described in the final report. The protocol compliance criteria are the following:

- Participants fulfilling the inclusion and exclusion criteria
- Participants who have respected the number of vaccination and the time-intervals between the vaccination:
  - V2: 1st vaccination: D0, interval V1+2 weeks (± 3days)
  - V7: 2nd vaccination D28 , interval V2+4 weeks (± 3 days)
  - V12: 3rd vaccination D56 , interval V5+4 weeks (± 3days)
  - V17: Post vaccination D84 , interval V12+4 weeks (± 7days)
  - V18: Last study visit D365 , interval V17+ 9months (± 14days)
  - Subjects having respected the number of blood samples for biological safety evaluation, as well as the intervals between blood samples on Days -14, 28, 56, 84 and 365 within their applicable intervals

[figure not shown]

**ii). Intention to treat:** All participants who have received at least one vaccine dose will be included in the analysis. However, if a participant is not vaccinated for reasons unrelated to the primary outcome measure and the participants' code was broken during the period of the study that participant will be excluded from further analyses. In the event a participant withdraws from the study due to side effects, the last observation will be carried forward in all subsequent analyses (Last Observation Carried Forward LOCF) of the primary outcome measure.

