## 8.4 Population used in analyses

The primary analysis will be conducted on all participants who have received at least one vaccine dose. Participants withdrawing for reasons related to the primary outcome measure, their last observation will be used in all subsequent analyses (LOCF).

Per protocol analysis of the secondary and exploratory outcome measures will be performed on all vaccinated subjects for whom serum samples are available.

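### Section 8.3.1 adds to the intention-to-treat definition an exception tied to code-breaking that is either redundant or removes dosed children, and that conflicts with section 8.4

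*Protocol*

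**What the plan says.** Protocol section 8.3.1 ii opens with a plain rule: "All participants who have received at least one vaccine dose will be included in the analysis". The following sentence qualifies it. It begins "However, if a participant is not vaccinated for reasons unrelated to the primary outcome measure" and ends, for a child who also meets the second condition, that the "code was broken during the period of the study that participant will be excluded from further analyses". Both conditions must be met.

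Section 8.4, which assigns populations to analyses, says: "The primary analysis will be conducted on all participants who have received at least one vaccine dose". It does not repeat the exception or refer to it.

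The individual code breaks that the protocol describes all concern safety:

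- The synopsis foresees unblinding for safety reasons.
- Section 3.5.1 has the Local Safety Monitor hold a sealed set of codes "for the event when emergency unblinding may be required", and section 5.2 says the same in substance.
- Under section 6.2.1 the Local Safety Monitor may act: "he will have the authority to unblind individual subjects".
- Under section 6.2.3, once the Grade 3 threshold is met, "a decision of individual un-blinding may then be made by DSMB through the Local Safety Monitor".

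The primary outcome appears in two forms. Section 7.1.1 lists, among other criteria, "Any Serious Adverse Event (SAE) occurring from the inclusion through out the study". Section 8.6.1 frames its hypothesis on serious adverse reactions.

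**The concern.** A safety population should be fixed by exposure: a child who has had a dose stays in. Here, membership can depend on two later facts, whether the code was broken and why a dose was missed. The first is tied to safety by the protocol's own provisions. The second is a judgement for which section 8.3.1 names no assessor, no timing and no blinding requirement. An exclusion of this kind could remove children who had events from the numerator and denominator of the primary analysis.

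The two sections also give different denominators for the same analysis, so a programmer following 8.3.1 and one following 8.4 could report different rates. Sections 3.1 and 8.7.1 use the Day 84 results to decide on the next trial. With 10 children per arm, one child matters.

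**Working it through.** **Step 1. What can the exception do?** The set already requires one dose.

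- Reading A: not vaccinated means never vaccinated. Such a child was never in the set, so the exception removes nobody and is redundant.
- Reading B: not vaccinated means that a later dose was not given. The exception then removes children whom the preceding sentence includes.

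The sentence opens as a contrast to the inclusion rule and speaks of further analyses. Both features favour B, but the text does not settle it.

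**Step 2. Compare with section 8.4.** Under A the two sections agree. Under B they disagree for any dosed child who meets both conditions: out under 8.3.1, in under 8.4.

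**Step 3. When is a missed dose unrelated to the primary outcome?**

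- If the outcome is any serious adverse event (7.1.1), a dose missed because of such an event is arguably related, and the child stays. Exclusion then needs a separate reason for the missed dose.
- If the outcome is serious adverse reactions (8.6.1), a dose missed because of an event judged not caused by the vaccine can be called unrelated, and the child can be excluded.

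**Step 4. Size, for one arm.** The arm size is from section 8.2: 3 × 10 = 30, which reproduces the stated total. The event counts are illustrative assumptions, and the child is taken to leave both numerator and denominator. Exact (Clopper-Pearson) 95% limits:

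- 1 of 10: lower limit 1 − 0.975^(1/10) = 0.0025; the upper limit solves (1−p)^10 + 10p(1−p)^9 = 0.025, giving p = 0.445. Result: 10% (0.3% to 44.5%).
- 0 of 9: upper limit 1 − 0.025^(1/9) = 0.336. Result: 0% (0% to 33.6%).
- With two affected children, 2 of 10 is 20.0% (2.5% to 55.6%). Excluding one gives 1 of 9, 11.1% (0.3% to 48.2%). Excluding both gives 0 of 8, 0% (0% to 36.9%).

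**Step 5. Effect on the section 8.6.1 test.** Upper binomial tail against 25%. The protocol states no significance level, so one-sided 0.05 and 0.025 are both assumed.

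| Kept | Tail | One excluded | Tail |
|---|---|---|---|
| 5 of 10 | 0.078 | 4 of 9 | 0.166 |
| 6 of 10 | 0.020 | 5 of 9 | 0.049 |

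At 0.05, neither row changes its decision. At 0.025, 6 of 10 rejects and 5 of 9 does not. The more direct effect is on the reported rate and interval.

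**The case against.** The strongest reply is that the sentence is only loose drafting. Reading A is a natural reading of the words, and on it nobody is lost. Section 8.4 already states the right population. Events would not vanish from view in any case: section 6.2.2 sends serious events to the DSMB whatever their relationship to vaccine, section 6.3.7 requires reports within 24 hours, and sections 3.5.3 and 3.5.4 seek continued safety follow-up when vaccination stops. This stands as far as it goes. It limits the harm to the analysed rates and to the few children who meet both conditions. It does not defend the sentence, which is useless under A and harmful under B.

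Three stronger readings are tempting, and the documents do not support them:

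- A reader might infer that the reason is judged after unblinding. The text gives no order and no assessor, and section 3.5.2 requires investigators and outcome assessors to be kept blinded. A judgement made with the allocation known is possible, not prescribed.
- A reader might infer that the single-blind stage after Day 84 makes every child's code broken. A planned change of blinding level is not clearly an individual code break, and section 3.1 places the primary analysis at the Day 84 data lock, before that stage.
- A reader might infer that any child with a serious event and a code break drops out. Under section 7.1.1 a dose missed because of that event is arguably related to the outcome, so the exception would not apply.

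**Conclusion.** The point holds as a defect of definition. The exception is either redundant or an exclusion after randomisation and dosing, conditional on a code break that the protocol ties to safety. In the second case it contradicts section 8.4.

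The possible size is one arm moving from 10% (0.3% to 44.5%) to 0% (0% to 33.6%). This rests on Reading B, on a single event in the arm, on a code break for that child, and on the missed dose being judged unrelated to the primary outcome, which is plausible mainly under the wording of section 8.6.1. The documents give no rate for this combination, and few children would be affected.

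The programme's own reports favour inclusion. In the adult trials described in section 1.7.4, one of 30 and one of 40 volunteers did not receive all three doses, yet all volunteers are said to be in the intention-to-treat interim analysis. No code break is reported in either, so these show practice on missed doses only.

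**What to change.** In section 8.3.1 ii, delete the sentence that begins "However, if a participant is not vaccinated for reasons unrelated to the primary outcome measure", so that the definition agrees with section 8.4. State that every child with one dose or more stays in all safety analyses, using all follow-up collected, whatever happened to the code or to later doses. List code breaks and missed doses by arm, with reasons. If the reduced set is wanted, show it only as a labelled sensitivity analysis.

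The cost is one sentence removed and one short listing added. No extra data are needed, since section 3.5.4 already asks for continued safety follow-up of children who stop.

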### 8.2 Determination of the Sample Size

The total number of participants will be 30 divided into three groups of 10 each; one receiving 30 µg of GMZ 2, another 100 µg of GMZ2 and the other receiving rabies vaccine (control vaccine). The sample size chosen for this study are in line with similar safety and immunogenicity studies of similar candidate malaria vaccines published in the literature. As a phase I protocol, this study of 30 volunteers is not designed to detect adverse reactions that occur infrequently. Sample size was determined by the requirement to make a preliminary evaluation of inter-group and inter-individual variability, to avoid excessive risk and to allow realistic workload. Statistical significance may not be reached in such a study with low power; however, a non-significant finding would provide justification of the need for a study with greater power.

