## 8.5 Specific analyses

As mentioned above, the last observation of participants withdrawing for reasons related to the primary outcome measure will be carried forward. The proportion of participants that received three vaccine doses without experiencing side effects will be estimated by the Kaplan-Meier product-limit method.

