## 8.6 Statistical Methods

The analysis shall be descriptive as the sample size does not allow any comparison between groups. For categorical variables, frequency distributions, by vaccination group, will be presented. For continuous variables, box-whisker plots, medians, inter-quartile ranges and ranges will be presented by vaccine group.

The proportion of participants that received three vaccine doses without experiencing (serious) side effects will be estimated by the Kaplan-Meier product-limit method, with time as a discrete variable.

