### 8.6.1 Primary Criterion

The null hypothesis for the primary outcome measure will be evaluated using a one-sample one-sided test for proportions. The null hypothesis states that the frequency of serious adverse reactions is equal among each of the three groups (30 µg GMZ2, 100 µg GMZ2 and rabies vaccinated group). The alternative hypothesis states that this frequency is greater than 25% in the GMZ2 groups.

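### LOCF for safety outcomes, a code-break exclusion that Section 8.4 does not share, and a Kaplan-Meier event worded two ways could distort the safety summaries or leave them undefined

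*Protocol*

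**What the plan says.** All references are to the protocol.

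- **Analysis set.** Section 8.4: "The primary analysis will be conducted on all participants who have received at least one vaccine dose". Section 8.3.1 also starts from at least one dose, but then removes a child who is not vaccinated for reasons unrelated to the primary outcome and whose "code was broken during the period of the study that participant will be excluded from further analyses". Section 8.4 does not repeat this.
- **LOCF.** Section 8.3.1: "In the event a participant withdraws from the study due to side effects, the last observation will be carried forward in all subsequent analyses", and it limits this to the primary outcome measure. Sections 8.4 and 8.5 restate the rule for withdrawals related to that outcome.
- **Kaplan-Meier.** Section 8.5: "The proportion of participants that received three vaccine doses without experiencing side effects will be estimated by the Kaplan-Meier product-limit method". Section 8.6 gives the same proportion, but "without experiencing (serious) side effects will be estimated by the Kaplan-Meier product-limit method, with time as a discrete variable".
- **Primary outcome.** Section 7.1.1 lists immediate reactions, reactogenicity over 14 days after each dose, medically attended events, any SAE during the study whether related or not, and laboratory values one month after each vaccination.
- **Follow-up after stopping.** Sections 3.5.3 and 3.5.4 plan continued safety surveillance of children who stop vaccination or withdraw.
- **Use of the results.** Section 8.7.1 plans a Day 84 analysis of adverse events by dose and number of vaccinations, to inform decisions on the next trial.

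**The concern.** LOCF was devised for a repeated measurement with a final value. Here the outcome is whether an event occurs after a given dose. A child who stops after dose 1 has no reaction to dose 2 or 3 to observe. Carrying a state forward either creates reactions to doses not given or credits tolerance of them. The text does not say which state is carried: the worst grade, or the finding at the last visit. Nor does it say whether data collected after withdrawal take precedence over a carried value.

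The exclusion in Section 8.3.1 contradicts Section 8.4. The two Kaplan-Meier sentences name different events for what appears to be one estimate. Neither section says how LOCF and censoring work together.

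At stake are the per-dose, severity and laboratory summaries at Day 84. The children affected are few, but with 10 per arm each one is 10 percentage points.

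**Working it through.** **Inputs.** Section 8.2: "The total number of participants will be 30 divided into three groups of 10 each", so 3 × 10 = 30. No power, alpha or dropout figure is stated, so there is no planned operating characteristic to reproduce. Section 8.6.1 names a "one-sample one-sided test for proportions" with 25% as the reference rate. All event counts below are hypothetical.

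**1. LOCF and per-dose rates.** In an arm of 10, k children have an event at dose 1 and withdraw, and nothing else happens. Doses given = 10 + 2(10 − k).

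| k | Per dose given | LOCF, event carried (3k/30) | LOCF, resolved state carried (k/30) | Children ever with event (k/10) |
|---|---|---|---|---|
| 1 | 1/28 = 3.6% | 10% | 3.3% | 10% |
| 2 | 2/26 = 7.7% | 20% | 6.7% | 20% |
| 3 | 3/24 = 12.5% | 30% | 10% | 30% |

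The last column is the same with or without LOCF. The per-dose rate rises or falls depending on a choice that the protocol does not make.

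**2. The exclusion.** It needs both conditions: not vaccinated for an unrelated reason, and code broken. If not vaccinated means never vaccinated, the child is already outside the at-least-one-dose set and the rule does nothing. It has an effect only if it means a missed later dose, for example after an SAE judged unrelated, which Section 7.1.1 still counts. Take one event in an arm of 10, with exact 95% intervals:

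- everyone kept: 1/10 = 10% (0.3-44.5%);
- the child with the event dropped: 0/9 = 0% (0-33.6%);
- a child without the event dropped: 1/9 = 11.1% (0.3-48.2%).

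It also shifts the exact tail probability against 25%: P(5 or more events) is 0.078 with n = 10 and 0.049 with n = 9.

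**3. The Kaplan-Meier event.** With no censoring and independent doses, the event-free proportion after three doses is (1 − p)³. Section 1.9.2 gives local reactions in 30%-74% of recipients of human diploid cell rabies vaccine; using these as per-dose rates is an assumption.

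- Any side effect: p = 0.30 gives 34.3%; p = 0.74 gives 1.8%. A lower assumed p = 0.10 gives 72.9%.
- Serious only, assumed p = 0 to 0.05: 100% to 85.7%.

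For p = 0.30 to 0.74 the two definitions differ by 85.7 − 34.3 = 51 to 100 − 1.8 = 98 points. At p = 0.10 they differ by 85.7 − 72.9 = 13 to 100 − 72.9 = 27 points.

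**4. LOCF alongside Kaplan-Meier.** Take the serious definition. In an arm of 10, two have an event at dose 1, one then withdraws for a non-serious reaction, two have an event at dose 2 and one at dose 3.

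- Withdrawal censored: (1 − 2/10)(1 − 2/7)(1 − 1/5) = 45.7%.
- Three doses received with no event: 4/10 = 40%.
- Withdrawal carried forward as event-free: 5/10 = 50%.

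The text does not choose among these three.

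**The case against.** The strongest reply is that little of this reaches the headline numbers. Section 8.6 declares the analysis descriptive, and under Section 6.2.3 the DSMB sees safety tables after each vaccination. LOCF applies only when a child withdraws because of side effects, which may be rare. Under the Section 8.5 event such a child has already failed, so LOCF and Kaplan-Meier conflict only under the serious definition, when the withdrawal was for a non-serious reaction. The parentheses in Section 8.6 may mean that both versions will be reported. All of this stands, and it limits the severity. It does not remove the text that prescribes LOCF or the disagreement between sections.

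A reader might infer more than the protocol supports:

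- *LOCF makes the primary safety rates wrong.* It does not alter the ever-event proportion per child, nor the Section 8.6.1 proportion with a serious adverse reaction.
- *A child unblinded for a vaccine reaction is dropped.* The exclusion also requires non-vaccination for an unrelated reason, so that child stays in.
- *The unrelated judgement is made with the arm known.* No section says so. Sections 3.5.2 and 6.3.2 keep the assessing investigators blinded. Section 8.3.1 does not say who judges the reason for non-vaccination, or whether that comes before the code-break.
- *The adult trial shows that the exclusion would be used.* Section 1.7.4.2 reports one of 40 missing dose 3 and five unrelated SAEs, but no broken code.
- *The Kaplan-Meier interval would be degenerate with no events.* The protocol names no interval method, and that can be left to the SAP.

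**Conclusion.** The point holds as a should-fix. LOCF for safety outcomes could distort per-dose, severity and laboratory summaries. In the illustration it moves a per-dose rate of 3.6-12.5% to 10-30%, or to 3.3-10%. The code-break exclusion contradicts Section 8.4 and, if it covers a missed later dose, can remove a countable SAE and move an arm from 1/10 to 0/9. The Kaplan-Meier estimate is left undefined; the gap between its two events ranges from about 13 to 98 points across the rates tried.

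The conflicts in the text need no assumption. The sizes rest on hypothetical counts in an arm of 10, independent doses and assumed per-dose rates. The effects arise only if a child withdraws because of side effects or meets both exclusion conditions, or once the Kaplan-Meier estimate is reported.

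**What to change.** 1. Delete LOCF for safety outcomes from Sections 8.3.1, 8.4 and 8.5. Use all observed safety data from every child with at least one dose, including data collected after stopping under Section 3.5.4. Give per-dose rates among children who received that dose, and overall rates as ever having had the event through last contact.
2. Delete the code-break exclusion so that Section 8.3.1 agrees with Section 8.4, and describe such children separately.
3. State one Kaplan-Meier event, with its censoring rule, identically in Sections 8.5 and 8.6, or report the two versions as separately named estimates. Kaplan-Meier need not be abandoned and no new endpoint is needed.

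The cost is a wording amendment before the Day 84 data lock. It needs no extra children, visits or samples, and the analysis becomes simpler.

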### 3.5.4 Handling of Withdrawals

Every effort will be made to collect safety data on any participant discontinued because of an AE or SAE by continuing the safety follow-up procedures. If voluntary withdrawal occurs, the participant will be asked to continue scheduled evaluations and be given appropriate care under medical supervision until the symptoms of any AE resolve or the participant's condition becomes stable. If possible, participants who leave the study area will be traced and visited by clinical investigators to collect all possible safety follow-up data.

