### 8.7.1 Plans for analysis

A final statistical analysis plan will be agreed upon by the investigators, AMANET and EMVI prior to locking of the database for the final analysis. However, an interim analysis is planned at 28 days post dose 3 (after day 84). This analysis will allow AMANET and EMVI make decisions for the next trial based on the immediate safety profile. This analysis will include information on adverse events by dose and number of vaccinations. Thereafter, the study will continue in a single blind manner for additional safety surveillance and immunogenicity assessment. This additional information will be appended to the study report.

It is anticipated that the results of this study will be presented to the scientific community via oral presentations at meetings and written publications in scientific journals. The data to be presented and the authorship will be discussed between investigators and the sponsor. It is AMANET policy to have the Principal Investigator lead the authorship for work arising from clinical trials, however, the draft manuscript has to be, approved by the sponsor and EMVI prior to any official communication.

The official report of the primary analysis will be submitted through appropriate channels and upon approval by AMANET. This report will contain detailed information about the participants, their tolerance of the vaccines, their side effects and laboratory abnormalities, as well as their overall immune responses to vaccination based on the ICH E-3 and E-9 format.

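### LOCF on the primary safety outcome supplies results for doses never given when a child leaves the study because of side effects

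*Protocol*

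**What the plan says.** Section 8.3.1(ii) includes every child with at least one dose in the intention-to-treat population. For a child who withdraws because of side effects, "the last observation will be carried forward in all subsequent analyses (Last Observation Carried Forward LOCF) of the primary outcome measure". Section 8.4 applies LOCF in the primary analysis to children who withdraw for reasons related to the primary outcome. Section 8.5 states it a third time: "the last observation of participants withdrawing for reasons related to the primary outcome measure will be carried forward". None of the three says whether the last observation is the last visit, the worst grade, or an ever/never status.

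The outcome under this rule is defined in Section 7.1.1. It covers immediate reactions after each injection, "Local and systemic reactogenicity measured from Day 0 to Day 14 after each dose", medically attended unsolicited events, serious adverse events, and haematology and biochemistry one month after each vaccination. On the Day 84 analysis, Section 8.7.1 says: "This analysis will include information on adverse events by dose and number of vaccinations".

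On withdrawals, Section 3.5.4 says: "Every effort will be made to collect safety data on any participant discontinued because of an AE or SAE". It also asks voluntary withdrawers to keep attending scheduled evaluations. Section 3.5.3 encourages children who may not be vaccinated further to stay under safety surveillance.

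**The concern.** LOCF stands in for a value that exists but was not observed. A reaction to dose 2 in a child who never received dose 2 does not exist, and no earlier record can represent it. Most of the primary outcome is of this kind: events tied to a particular injection, or laboratory values tied to a particular interval after one.

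Because the primary analysis takes everyone with at least one dose, partly vaccinated children are in it. A table by number of vaccinations is where carried values would enter. The rule acts only on children who left because of toxicity, and they matter most to the primary objective. The Day 84 results feed the decision on the next paediatric trial (3.1, 8.7.1).

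**Working it through.** The plan gives no figure to reproduce here. Its total of 30 is 3 × 10 and is not derived from power or from an expected withdrawal rate (8.2). The check is therefore a count.

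**Inputs**
- n = 10 children per arm (8.2).
- Analysis set: all children with at least one dose (8.4).
- k = children in one arm who leave the study and its follow-up because of a reaction to dose 1. Assumed.
- m = children among the remaining n − k who react to a later dose, say dose 3. Assumed.

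**Formulas for the dose 3 reaction rate**
- Children given dose 3: m/(n − k)
- LOCF, last record resolved: m/n
- LOCF, last record still reacting: (m + k)/n
- Gap between the two LOCF readings: k/n, which is 10 percentage points per child when n = 10

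| k | m | Children given dose 3 | LOCF, resolved | LOCF, reacting | Any reaction, per child |
|---|---|---|---|---|---|
| 1 | 0 | 0/9 = 0% | 0/10 = 0% | 1/10 = 10.0% | 1/10 |
| 1 | 1 | 1/9 = 11.1% | 1/10 = 10.0% | 2/10 = 20.0% | 2/10 |
| 2 | 2 | 2/8 = 25.0% | 2/10 = 20.0% | 4/10 = 40.0% | 4/10 |
| 3 | 2 | 2/7 = 28.6% | 2/10 = 20.0% | 5/10 = 50.0% | 5/10 |

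The last column counts the k dose 1 reactors plus the m dose 3 reactors, and assumes no other reactions.

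The resolved reading never exceeds the rate among children given the dose, and the reacting reading never falls below it. The direction of the error therefore depends on when the last record was made. In the first row the exact 95% interval is 0 to 33.6% for 0/9 and 0.3 to 44.5% for 1/10. The second reports a dose 3 reaction in a child who had no dose 3.

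**Laboratory values.** A child who leaves after the Day 28 sample has no value one month after doses 2 and 3. LOCF repeats the Day 28 value at Days 56 and 84, normal or abnormal, and that copy enters the medians and ranges planned in Section 8.6.

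**How often this might arise.** In the earlier GMZ2 trials 29 of 30 adults (1.7.4.1) and 39 of 40 adults (1.7.4.2) received all three doses. One exception was for reasons unrelated to vaccination and the other was pulmonary tuberculosis. That is 0 of 70 missing a dose because of a vaccine reaction, with an exact upper 95% limit of 1 − 0.025^(1/70) = 5.1%. At that limit an arm of 10 would expect 10 × 0.051 = 0.5 such children. These were adults, and the 40 include rabies-vaccine controls, so this is only a rough guide for children aged 1 to 5.

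**The case against.** The strongest reply is that the rule will seldom bite. In Section 8.3.1 it is triggered when "In the event a participant withdraws from the study due to side effects, the last observation will be carried forward in all subsequent analyses", that is, by leaving the study. Sections 3.5.3 and 3.5.4 try to keep children who stop vaccination under observation, and those who stay have observed data. The earlier GMZ2 trials show no dose missed because of a vaccine reaction. The analysis is mainly descriptive, and intervals at 10 per arm are wide in any case. All of this stands and limits how often the problem occurs. It does not make the rule valid for the children to whom it applies.

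Three stronger readings are tempting, and the documents do not support them.
- A reader might infer that the most reactive child will be counted as tolerating later doses. That is one of two outcomes. The protocol does not define the last observation, and a child who leaves while reacting would be carried forward as reacting.
- A reader might infer that the last record will usually be resolved, since Section 6.3.6 follows events in children withdrawn for an adverse event, and Section 6.3.1 calls local reactions usually mild and transient. No figure supports usually, and Section 6.3.6 also lets follow-up end at stabilisation or loss to follow-up.
- A reader might infer that the test of serious adverse reactions against 25% (8.6.1) is distorted. If each child is scored as ever or never having had one, an event already recorded stays counted and LOCF does no harm.

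**Conclusion.** The point holds for reaction rates by dose and for laboratory summaries, in children who leave both vaccination and follow-up because of side effects. For them the plan as written reports results that do not exist. The error is up or down depending on an undefined last record, with 10 percentage points per child between the two readings in a 10-child arm. How many children this would involve is not stated, so the tabulated k and m are illustrations. If no child leaves for this reason, nothing changes.

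It should be fixed, but it does not undermine the trial. Three sections state the rule outright, so a statistical analysis plan consistent with the protocol would inherit it.

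**What to change.** Delete LOCF from Sections 8.3.1(ii), 8.4 and 8.5, and state instead:
- Reactions for each dose are reported as observed, with the children who received that dose as denominator.
- The worst grade over doses received is reported for all children with at least one dose, so a child withdrawn for a side effect counts as having had it.
- Withdrawals because of side effects are reported as a separate count by arm.
- Laboratory values are reported as observed, with the number missing at each time point.
- In the Kaplan-Meier estimate of completing three doses without side effects (8.5, 8.6), a side-effect withdrawal counts as an event, not as event-free or censored.

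The cost is a few sentences in three sections, carried into the statistical analysis plan that Section 8.7.1 requires before database lock. No additional data, visits or participants are needed.
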